### Data monitoring

Data will be accessible to the trial investigators (JB, SM, AG, ST, PM) and will be stored on a password-protected computer (JB) and uploaded to LabArchives, a secure cloud-based server. This study will have a Trial Management Committee that will be comprised of study investigators (JB, SM, AG, ST, PM). The Committee will meet every 4 weeks to review safety reports, data quality, protocol adherence and retention rates. An independent Data Monitoring and Ethics Committee was considered to not be needed for this trial, as it is relatively short and includes two safe and common interventions [14]. In addition, the participants are not considered to be vulnerable [59, 60]. There will be no formal interim analysis.

### Statistical analysis

Statistical analysis will be performed using the most recent version of SPSS (IBM Corp., Armonk, NY, USA) available at the time of analysis. Data will be double entered to minimise errors. Demographic data and anthropometric characteristics (e.g. gender, age, foot posture using the FPI, etc.) will be reported by the treatment arm.

The intention-to-treat principle will be used for all participants [61]. Multiple imputation will be used to replace missing data for the primary and secondary outcome measures [62], with the exception being ‘Global Rating of Change Scale, where no data substitution will be applied. Standard tests to assess continuous data for normal distribution will be used and transformation performed if required. The primary outcome measure assessed will be pain intensity (at its worst) at 12 weeks. Continuously scored outcome measures (pain intensity (NRS-11), VISA-A, LEFS, EuroQol 5—VAS, IPAQ-SF and biomechanical outcomes) will be analysed using an ANCOVA with adjustment for baseline scores [63].

Dichotomous data (Global Rating of Change Scale, adverse events and use of co-interventions) will be compared using relative risk, absolute risk increase and number needed to treat or harm. Intervention adherence and CEQ data will be compared between groups using independent *t*-tests. To complement point estimates, standard deviations, 95% confidence intervals and *p*-values will be calculated where appropriate.

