**Methods:**

One hundred and eight men and women aged 18 to 65 years with mid-portion Achilles tendinopathy (who satisfy the inclusion and exclusion criteria) will be recruited. Participants will be randomised, using the website Sealed Envelope, to either a control group (sham heel lifts) or an experimental group (heel lifts). Both groups will be provided with education regarding acceptable pain levels to ensure all participants receive some form of treatment. The participants will be instructed to use their allocated intervention for at least 8 h every day for 12 weeks. The primary outcome measure will be pain intensity (numerical rating scale) at its worst over the previous week. The secondary outcome measures will be additional measures of Achilles tendon pain and disability, participant-perceived global ratings of change, function, level of physical activity and health-related quality of life. Data will be collected at baseline and the primary endpoint (week 12). Data will be analysed using the intention-to-treat principle. In addition, the acute kinetic and kinematic effects of the interventions will be examined at baseline in a subpopulation of the participants (*n* = 40) while walking and running using three-dimensional motion analysis.

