### Outcomes

Primary and secondary outcome measures [35] will be collected at baseline and at 12 weeks (the endpoint). A summary of the data collection time points for each of the outcome measures is shown in Fig. 3. Follow-up data will be collected using REDCap™ surveys; however, participants will have the option of a postal survey. Where participants have bilateral symptoms, they will be asked to report for their most painful side (or right side, if the Achilles tendons are equally painful) to maintain independence of data [36, 37].

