#### Primary outcome

The primary outcome will be pain intensity at its worst in the previous week using a 11-point numerical rating scale (NRS) with terminal descriptors of ‘no pain’ (score = 0) and ‘worst pain possible’ (score = 10) [38]. This outcome was chosen as it is a core domain in the consensus statement for tendinopathy [35].

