#### Other outcomes

##### Co-interventions

The use of co-interventions to relieve pain at the Achilles tendon will be measured at 4, 8 and 12 weeks via a REDCap survey™. The use of paracetamol rescue medication (number of participants and mean consumption) or any other treatment (e.g. exercise) to manage their Achilles tendon pain.

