##### Adverse events

Adverse events from the interventions (such as skin blistering or the occurrence of new pain or injuries in other areas of the foot and body) will be assessed at 4, 8 and 12 weeks via a REDCap survey™. Participants will be asked to document the type of adverse event, the body location, the duration and severity of the event [44]. An open-response type format will also be available for participant responses.

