##### Adherence

Adherence will be measured at 4, 8 and 12 weeks via a REDCap survey™. Participants will be asked to provide information regarding the average number of hours per day and number of days they have worn the heel lifts during the preceding 4 weeks.

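### Pain is scored only at baseline and week 12, so the planned multiple imputation has no interim pain score to draw on; one item added to the week-4 and week-8 surveys would reduce possible dropout bias

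*Protocol article*

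**What the plan says.** The primary outcome is "pain intensity at its worst in the previous week using a 11-point numerical rating scale (NRS"). Under Outcomes, the primary and secondary measures "will be collected at baseline and at 12 weeks (the endpoint"). The abstract agrees: "Data will be collected at baseline and the primary endpoint (week 12").

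Participants are nevertheless surveyed in between:
- Adherence: "Adherence will be measured at 4, 8 and 12 weeks via a REDCap survey".
- Co-interventions, including paracetamol: "The use of co-interventions to relieve pain at the Achilles tendon will be measured at 4, 8 and 12 weeks".
- Adverse events: these "will be assessed at 4, 8 and 12 weeks via a REDCap survey".

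None of the three descriptions includes the pain score.

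For missing data, Statistical analysis says "Multiple imputation will be used to replace missing data for the primary and secondary outcome measures", with the Global Rating of Change excepted. Continuous outcomes "will be analysed using an ANCOVA with adjustment for baseline scores". The variables in the imputation model are not named. Sample size allows for dropout: 99 participants plus 9, giving 108.

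**The concern.** Imputation can improve on a complete-case analysis only if it uses information about the missing value that the analysis model does not already hold. Here the main analysis already conditions on arm and baseline pain. The secondary outcomes share the single week-12 follow-up, so a participant who is lost altogether lacks those too. What remains after baseline is non-pain information from the interim surveys and the credibility/expectancy score taken after allocation.

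At stake is bias in the primary comparison if loss depends on how pain evolves and does so differently in the two arms. Participants must have pain above 3 out of 10 at entry and agree to forgo other treatment, and one arm wears a sham, so pain-related loss is conceivable. An interim pain score would be the natural predictor of the missing week-12 value. Surveys already go out at suitable times, and a score not collected then cannot be recovered later by any analysis plan.

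**Working it through.** **1. The plan's own figure.** Inputs from Sample size: difference 1.5, SD 2.3, f = 0.33, power 90%, alpha 0.05. Check: f = 1.5 / (2 × 2.3) = 0.326, stated as 0.33. With a noncentral F (one covariate, noncentrality f² × N), the smallest N reaching 90% is 99 (power 0.9016), as stated. The allowance of 9 is 9/108 = 8.3% of those recruited. The sample size is not in question; 8.3% serves below as the planned dropout.

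**2. Why imputing from arm and baseline adds nothing.** Let X hold the intercept, arm and baseline pain, and let b be the complete-case ANCOVA coefficients. Averaged over many imputations, each missing outcome is replaced by its prediction from b. Refitting to the completed data gives

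(X'X)⁻¹(X_obs'y_obs + X_mis'X_mis b) = (X'X)⁻¹(X_obs'X_obs + X_mis'X_mis) b = b.

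The estimate is the complete-case one, apart from noise due to a finite number of imputations.

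**3. Simulation.** From the documents: 54 per arm, SD 2.3, true difference -1.5. Assumed, because the documents do not give them: pain correlations with week 12 of 0.40 (baseline), 0.60 (week 4) and 0.75 (week 8), and the dropout mechanisms. There were 600 trials per scenario at 8.3% dropout overall.

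| Dropout mechanism | Complete case | MI: arm + baseline | MI: + week-4/8 pain |
|---|---|---|---|
| Driven by week-8 pain, same direction in both arms, one common rule | -1.40 | -1.40 | -1.48 |
| Driven by week-8 pain, opposite directions by arm | -1.80 | -1.80 | -1.53 |

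The first two columns differ within a trial by 0.013 to 0.014 points on average. The Monte Carlo error of a mean is about 0.44/√600 = 0.018.

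In the first row the common rule still produces unequal loss, because the heel-lift arm has less pain by week 8. When the same mechanism is applied with 8.3% lost in each arm, complete case gives -1.49, which is no bias.

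A third pattern assumes 11% sham dropout driven by week-8 pain and 4% heel-lift dropout at random. Complete case and baseline-only imputation both give -1.34 (4,000 trials), and adding week-8 pain gives -1.50. Varying how strongly pain drives dropout moves the complete-case result between -1.38 and -1.27.

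**4. What the interim data already planned could recover.** This uses one non-pain auxiliary with assumed correlation r with pain, in the opposite-direction scenario.
- r = 0.3: -1.804 becomes -1.762. Against the full-data value of -1.524 in the same trials, 0.042/0.280 = 15% of the bias is removed.
- r = 0.5: -1.806 becomes -1.691. Against -1.5, 0.115/0.306 = 38% is removed.

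**5. Limits of the added item.** Same opposite-direction mechanism, separate runs.
- Half of dropouts lost before week 4: -1.764 becomes -1.622, so the bias falls from 0.264 to 0.122 and about half remains.
- All lost before week 4: -1.770 becomes -1.771, so nothing is gained.

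**6. Precision.** With dropout completely at random, the standard error is 0.423 (complete case), 0.424 (arm + baseline) and 0.415 (with week-4/8 pain). The gain is 1 - 0.415/0.423 = 1.9%.

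**The case against.** The strongest reply is that the article does not name the imputation model. Auxiliary variables are commonly left to an analysis plan, which is not shown. A reader might infer that a lost participant has nothing but baseline values to impute from, or that the planned imputation must equal the complete-case analysis. The documents support neither. Interim adherence, co-intervention and adverse-event data will exist, as will the credibility/expectancy score. A participant who skips the pain item at week 12 but answers other questionnaires also gives the imputation something to use. The equality in step 2 is therefore conditional on a model with arm and baseline pain. What stands against this reply is the schedule, which this document does fix: no analysis plan can use an interim pain score that was never collected, and the non-pain data recover a minority of the bias under the assumed correlations.

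Second, a single 12-week endpoint matches the stated aim and contradicts nothing. That is correct, so the point is a design improvement.

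Third, the bias depends on assumed dropout. Both arms receive a take-home insert and the same education, and nothing in the article shows that loss will be unequal. Even the sign changes with the mechanism. That stands, and it is why a range is given. A reader might also infer that the primary result will be biased; the documents do not show this.

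Fourth, recruitment began in July 2023 and was expected to end in December 2024, so an item added mid-trial would be missing for earlier participants. That also stands and reduces the benefit.

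**Conclusion.** The point holds as a cheap improvement. Pain is collected at baseline and week 12 only, so imputation from arm and baseline pain adds nothing to the complete-case ANCOVA, and the interim data already planned probably recover only a minority of any dropout bias. With about 8 to 11% dropout, the bias runs from zero under equal, same-direction loss to roughly 0.1 to 0.3 points in either direction under differential pain-related loss. The upper end is 0.3/0.42, or about 0.7 of a standard error. These sizes rest on the assumed correlations and dropout mechanisms.

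It would be too strong to say that an interim pain item cures the problem. It helps only those who answer at week 4 or 8 before being lost, and only if data are missing at random given those scores. Dropout that depends on unobserved week-12 pain is untouched. The gain in precision is about 2%, so the case rests on protection against bias.

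**What to change.** Add the single 0-10 item on worst pain in the past week to the REDCap surveys already sent at weeks 4 and 8. Keep week 12 as the sole primary endpoint and the baseline-adjusted ANCOVA as the analysis. In the imputation model, use week-4 and week-8 pain as auxiliary variables, together with the adherence, co-intervention and adverse-event data from the same surveys. State that the interim scores are there to support imputation and are not additional endpoints.

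The cost is one question in each of two existing surveys, slight participant burden, and a minor ethics and registry amendment. Sample size, visits and treatment do not change. Participants already past those surveys will lack the item, and the report should say how many. If the amendment is no longer practical, the existing interim data can still be used as auxiliaries, with a clear statement that they offer limited protection.

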### Sample size

The sample size has been determined a priori using G*Power [55] based on pain intensity at its worst in the previous week as the primary outcome measure. We calculated the sample size using an *f*-test, analysis of covariance (ANCOVA). Using an allocation ratio of 1:1, 90% power, minimal clinically important difference of 1.5 units out of 10 [56], standard deviation of 2.3 [14], moderate effect size [57] (*f* = 0.33) and a significance level set at *a* < 0.05, we estimate that a total of 108 participants will be required (99 and an extra 9 for 10% drop-out) [58].

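### A normality-test rule could move the primary pain analysis off the 0–10 NRS scale on which the 1.5-point MCID and the sample size are defined

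*Protocol article*

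**What the plan says.** All references are to the protocol article.

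- **Statistical analysis**, the rule: "Standard tests to assess continuous data for normal distribution will be used and transformation performed if required".
- **Statistical analysis**, its reach: the outcomes treated as continuous are "Continuously scored outcome measures (pain intensity (NRS-11), VISA-A, LEFS, EuroQol 5—VAS, IPAQ-SF and biomechanical outcomes"; these "will be analysed using an ANCOVA with adjustment for baseline scores". Pain NRS comes first in the list. Nothing exempts it from the rule, and nothing says the difference in NRS points will be reported regardless.
- **Primary outcome**: "pain intensity at its worst in the previous week using a 11-point numerical rating scale (NRS". It is an integer score from 0 to 10.
- **Sample size**: the calculation uses a "minimal clinically important difference of 1.5 units out of 10" and a "standard deviation of 2.3". Both are in untransformed NRS points.

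The Eligibility criteria also require worst pain above 3 out of 10 at entry, which truncates the baseline score.

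**The concern.** The Sample size section defines a worthwhile effect in NRS points. The Statistical analysis section then allows a test on the observed data to decide whether the primary outcome stays in NRS points. Three things follow.

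1. The rule speaks of testing the data. The ANCOVA assumption concerns the residuals, and with about 50 per arm even that matters little for the test of a mean difference.
2. An 11-value score bounded at 0 and 10 is easily flagged as non-normal, so the rule has a real chance of being invoked.
3. After a log or root transformation the treatment effect is a ratio or a root-scale difference. It cannot be read directly against 1.5 points, and back-transforming does not return a mean difference in points. A log also needs an added constant if any score is 0.

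At stake are the interpretability of the primary estimate and a choice of scale made after the outcome is seen.

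**Working it through.** **1. The plan's own figure, to establish its scale.** With two equal groups, f = difference / (2 × SD) = 1.5 / (2 × 2.3) = 0.326, which the article gives as 0.33. For ANCOVA with one covariate, power comes from the noncentral F with 1 and N − 3 degrees of freedom and λ = f² × N. At N = 99, λ = 0.33² × 99 = 10.8 and power is 0.902. The stated 99 is reproduced exactly, and it is a calculation on the untransformed NRS. (With f unrounded at 0.326, N is 101.)

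**2. How often would a normality test reject?** The documents give no week-12 means, baseline distribution or baseline correlation, so these are assumptions: week-12 means of 2 to 5, and scores drawn from a normal distribution with SD 2.3, then rounded and clipped to 0–10. Where baseline enters the model it is centred near 6, restricted to 4–10, with a slope of 0.4. Rejection rates at the 5% level (Shapiro-Wilk / Lilliefors):

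| What is tested | Mean 2 | Mean 3 | Mean 4 | Mean 5 |
|---|---|---|---|---|
| Pooled raw scores, n = 99 | 100% / 100% | 100% / 100% | 99% / 99% | 88% / 99% |
| One arm, n = 50 | 100% / 99% | 89% / 81% | 39% / 66% | 22% / 65% |
| ANCOVA residuals, n = 100, 1.5-point effect (mean = control arm) | 96% / 97% | 69% / 64% | 26% / 22% | 9% / 14% |

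Further runs with 49 per arm and slightly different baseline assumptions widen the ranges to about 85–100% for pooled raw scores (Shapiro-Wilk) and about 4–97% for residuals. Truncated baseline scores reject in 98–100% of trials, but baseline is the covariate and ANCOVA does not require it to be normal.

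**3. Is raw-scale ANCOVA valid here?** With 98 participants, control means of 3, 4 and 5 and 5,000 simulated trials each:

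| | Mean 3 | Mean 4 | Mean 5 |
|---|---|---|---|
| Type I error, raw NRS | 4.8% | 5.3% | 5.2% |
| Power, raw NRS | 89.6% | 89.9% | 90.9% |
| Power, log(NRS + 1) | 87.4% | 88.2% | 88.0% |
| Power, square root | 87.8% | 89.3% | 88.9% |

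The simulation error on a 5% rate is √(0.05 × 0.95 / 5,000) = 0.3 percentage points, so the type I error is at its nominal level. Across all runs, raw ANCOVA had type I error of 4.1–5.5% and power of 90–93%.

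**4. What does the two-step rule do to inference?** Testing first and taking log(NRS + 1) on rejection gave type I error of 4.6–5.7% and power of about 90–93%. This is practically the same as raw ANCOVA.

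**5. What happens to the 1.5 points?** On the log(NRS + 1) scale, a fall of 1.5 points is ln(start + 1) − ln(start − 0.5):

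- from 6: ln 7 − ln 5.5 = 0.24 (ratio 0.79)
- from 5: ln 6 − ln 4.5 = 0.29 (ratio 0.75)
- from 4: ln 5 − ln 3.5 = 0.36 (ratio 0.70)
- from 3: ln 4 − ln 2.5 = 0.47 (ratio 0.625)

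The same 1.5 points is almost twice as large on the log scale from 3 as from 6, so the MCID has no single equivalent there.

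**The case against.** The best defence is that the rule is conditional. It names no test, threshold or automatic trigger. A sensible analyst would look at residuals, where rejection can be as low as about 4%. A common descriptive criterion, absolute skewness above 1, was met in at most 1% of trials simulated with control means of 3 to 5. Type I error and power hardly move. Even picking the smallest p-value from raw, log and square-root analyses raised type I error only to about 7%, and nothing in the article suggests such picking. Which test, which transformation and what back-transformation are details that an article may leave to the SAP.

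Much of this stands. The missing details are not counted here as faults, and no material loss of validity is claimed. Two stronger readings that a reader might infer are not supported:

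- **That the rule will almost always be triggered.** This fits pooled raw scores under the assumed means. It does not fit single arms with mid-scale means (22–66%) or residuals, and a significant test does not by itself oblige anyone to transform.
- **That the trial could not say whether heel lifts reach the MCID.** Nothing prevents the authors from also reporting means and differences in NRS points, and the article promises point estimates with confidence intervals. The MCID appears only as a sample-size input.

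What the defence does not remove is that the article states a positive rule, applies it to the primary outcome without exemption, and so leaves the scale of the primary effect open until the data are in. A SAP that fixed the raw scale would have to override this sentence. That the trigger rate runs from about 4% to 100% depending on what is tested shows how little the rule settles.

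**Conclusion.** The point holds as a weakness in how the primary analysis is fixed. The primary result could move to a scale on which 1.5 points has no single equivalent, and that choice would follow inspection of the data. The likelihood depends on what is tested: about 85–100% rejection for pooled raw scores, and about 4–97% for ANCOVA residuals. The harm is to interpretability and pre-specification. Inference stays sound, since type I error remains near 5% and the log transformation costs only about 1 to 3 points of power. Transformation brings no material gain, because raw-scale ANCOVA at about 50 per arm already performs as planned. The sample size is not in question.

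The rejection rates and power figures rest on assumed week-12 means, baseline distribution and correlation. The conflict between the rule and the scale of the MCID does not. Only the primary outcome was examined; the simulations say nothing about VISA-A, LEFS, EQ-VAS or IPAQ-SF.

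**What to change.** Add one sentence to the Statistical analysis section, and carry it into the SAP: the primary analysis is a baseline-adjusted ANCOVA of week-12 worst pain on the untransformed 0–10 NRS, whatever its distribution, reported as the adjusted mean difference in NRS points with its 95% CI.

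State also that model assumptions will be judged on residuals, and that any transformation, robust or bootstrap method for the primary outcome is a pre-specified sensitivity analysis only. If a bootstrap is chosen, say how it is combined with the planned multiple imputation. Which sensitivity method to use, and whether to keep a transformation rule for the other continuous outcomes, is for the authors to decide.

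The cost is wording only: no new data, N unchanged at 99 evaluable and 108 recruited. It is a free improvement, best made before the week-12 data are examined.

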### Objectives

The primary aim is to examine the efficacy of heel lifts versus sham heel lifts on pain intensity among individuals with mid-portion Achilles tendinopathy at 12 weeks. The secondary aim is to investigate the acute biomechanical effects of heel lifts among individuals with mid-portion Achilles tendinopathy.

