#### Sham intervention (control group)

Participants allocated to the control group will receive a pair of the sham heel lifts. The following sham intervention may be used; however, we will pilot other interventions (i.e. made of different materials and dimensions) prior to the trial and reserve the right to change the design if required (this will be reported as a change in the protocol on the website trial registration). The intended design of the sham intervention is to not plantarflex the ankle joint but appear as identical to the heel lifts as possible. To achieve this, the sham heel lift will extend the entire length of the shoe and will be made of the same materials as the heel lift (i.e. 1 mm of clear vinyl with a 3.2-mm PPT Ultralux top cover) (Fig. 2). This sham heel lift is necessary in this trial due to participant’s expectation of receiving a ‘take-home’ intervention (i.e. minimises resentful demoralization [30]). The sham intervention will be sized according to shoe size and trimmed (if needed) to fit into the participant’s footwear. Participants will be shown how to use the sham intervention and asked to wear them for at least 8 h every day.

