### Biomechanical assessment

At baseline, a subpopulation of participants who volunteer (*n* = 40) will undergo a biomechanical assessment to evaluate the acute changes in the biomechanical function of the Achilles tendon as this is the proposed mechanism of action of heel lifts. The variables of interest are Achilles tendon load (ATL), ankle joint moments and plantar/dorsiflexion range of motion (ROM), stance phase duration (SPD), ground reaction force (GRF) and tibial acceleration. One researcher (JB) will perform the assessment, with the support of experts in biomechanical analysis (ST, AG).

After completing a standardised and progressive 7-min warm-up, participants will be asked to walk (5 min) and run (3.5 min) with and without their allocated intervention (i.e. heel lift or sham heel lift) in four testing conditions: (i) walking, shoe only; (ii) walking with the allocated intervention; (iii) running, shoe only and (iv) running with the allocated intervention. The footwear used in testing will be standardised, using the same zero drop Merrell® shoe. The testing sequence will be randomised by a single author (JB). The gait conditions will be fixed at the participant’s optimal walking and preferred running speed to minimise the effect on biomechanical parameters [45].

Optimal walking speed (*V*) will be calculated to be a fourth of maximal walking speed, using the following calculation: *V* = sqrt(*L* × *g* × 0.25) [46]. The formula is based on the Froude number (0.25), leg length (*L*) and acceleration of gravity (*g*). Preferred running speed will be determined using a previously outlined method [47, 48]. Speed will be increased in increments of 0.1 km/h until they first report they have exceeded their preferred ‘comfortable’ running pace. Speed will then be decremented by 0.1 km/h until the participant has confirmed that their ‘comfortable’ running speed has been passed going down. This procedure will be repeated three times and speeds will be averaged to determine the preferred running speed. In between testing, participants will be given as long as required to recover and withdraw if pain exceeds 5 out of 10 on a VAS at any time during the trials [31].

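### The stated biomechanical ANCOVA gives lift minus sham; alone it neither estimates the lift against the shoe alone nor checks sham neutrality, though the data for both are collected

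*Protocol article*

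**What the plan says.** Objectives (protocol article): "The secondary aim is to investigate the acute biomechanical effects of heel lifts among individuals with mid-portion Achilles tendinopathy". The primary aim names sham heel lifts as its comparator; this one names none. The Methods paragraph of the Abstract uses the plural: "the acute kinetic and kinematic effects of the interventions will be examined at baseline".

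Biomechanical assessment: "a subpopulation of participants who volunteer (*n* = 40) will undergo a biomechanical assessment", and these "participants will be asked to walk (5 min) and run (3.5 min) with and without their allocated intervention". This gives a shoe-only and a with-insert condition for each gait, in a standardised zero-drop shoe and in randomised order.

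Sham intervention (control group): "The intended design of the sham intervention is to not plantarflex the ankle joint but appear as identical to the heel lifts as possible". The section allows for piloting and redesign of the sham before the trial. It describes no biomechanical test of neutrality.

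Statistical analysis: "EuroQol 5—VAS, IPAQ-SF and biomechanical outcomes) will be analysed using an ANCOVA with adjustment for baseline scores". No other analysis of the biomechanical variables is stated, and the section does not say what the baseline score is for variables that are all recorded at baseline.

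**The concern.** The substudy collects two kinds of information: how each device changes gait relative to the shoe alone, and how the two devices differ. The stated analysis reports only the second. If lift and sham turn out similar, the ANCOVA cannot say whether the lift does little or the sham does something comparable. If they differ, it cannot say which device moved.

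This matters because the Discussion paragraph of the Abstract promises insight into how heel lifts work, and the Background proposes that they reduce Achilles tendon load. A real load reduction could be masked by a sham effect in the same direction. A sham effect in the opposite direction could be credited to the lift.

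A smaller point is that the baseline-adjustment wording fits the 12-week questionnaires. For the biomechanical variables it makes sense only if baseline means the shoe-only condition, and the text does not say so.

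**Working it through.** The plan gives no power or precision figure for the 40 biomechanical volunteers, so there is no stated number to reproduce. The check concerns what the ANCOVA coefficient estimates.

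**Inputs from the article.** Two arms allocated 1:1; 40 volunteers; shoe-only and with-insert conditions for walking and for running; ANCOVA with baseline adjustment.

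**Assumptions, not in the documents.** 20 volunteers per arm; volunteering unrelated to arm; effects in between-person SDs; correlation r between the shoe-only and with-insert values of 0.7 to 0.9; shoe-only value used as the covariate.

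**Estimand.** Let X be the shoe-only value and Y the with-insert value. Let L and S be the mean effects of lift and sham against the shoe alone.

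- ANCOVA coefficient = (mean Y, lift - mean Y, sham) - b x (mean X, lift - mean X, sham). With no expected difference between the arms in X, its expectation is L - S.
- Within-arm contrast = mean of (Y - X). Its expectation is L in the lift arm and S in the sham arm.

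So the ANCOVA coefficient equals L only when S = 0, and the stated analysis does not examine S.

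**Simulation.** 4,000 runs per row, r = 0.8:

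| True L | True S | ANCOVA mean | ANCOVA rejects | Lift-arm mean (Y - X) | Sham-arm mean (Y - X) |
|---|---|---|---|---|---|
| -0.5 | 0 | -0.50 | 72% | -0.50 | 0.00 |
| -0.5 | -0.25 | -0.24 | 23% | -0.49 | -0.25 |
| -0.5 | -0.5 | 0.00 | 5% | -0.50 | -0.50 |
| 0 | +0.5 | -0.50 | 73% | 0.00 | +0.50 |

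Rows 1 and 4 give the same ANCOVA result from opposite situations. In row 3 the ANCOVA sees nothing, although the lift-arm contrast rejects zero in 92% of runs. The within-arm contrasts tell the rows apart.

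**What a sham-arm estimate could show.** The 95% CI half-width of a within-arm contrast is t(19) x sqrt(2(1 - r)/20), with t(19) = 2.093:

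- r = 0.7: 2.093 x sqrt(0.6/20) = 0.36 SD
- r = 0.8: 2.093 x sqrt(0.4/20) = 0.30 SD
- r = 0.9: 2.093 x sqrt(0.2/20) = 0.21 SD

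A sham-arm interval centred on zero would therefore still allow effects of about 0.2 to 0.4 SD. It informs the question of neutrality without proving it.

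**The case against.** The strongest reply is that lift versus sham is the right mechanistic contrast. The pain result is itself lift minus sham, the arms are randomised, and the secondary aim names no comparator, so reading it as lift versus sham is defensible. Both devices also carry the same 3.2-mm cover. Lift minus shoe-only therefore mixes heel elevation with the cover and with having any insert in the shoe, and the ANCOVA removes at least part of that. All of this stands. It is why the ANCOVA should be kept and why the lift-arm estimate needs a caveat.

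The general warning against within-arm comparisons in randomised trials has less force here. It concerns before-after change confounded with natural history, whereas these are acute conditions tested in randomised order.

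The section does not name the contrast or exclude others, the article is condensed, and an analysis plan that is not shown may add the within-arm estimates. A reader might infer that the sham's neutrality will never be examined. The article does not support that: it supports only that no such estimate is stated. The sham is also full-length, so it is built to avoid raising the heel relative to the forefoot, and it is to be piloted. The article gives no ground for presuming that it is active.

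**Conclusion.** The point holds as a mismatch between the data collected and the one analysis stated for them. The ANCOVA is valid, but its coefficient is L - S. Used alone, it leaves both the lift's effect against the shoe alone and the sham's effect unestimated. That identity does not depend on the assumed arm sizes or correlation; the simulated rates and interval widths do. That lift versus sham is the intended contrast is inferred from a baseline-adjusted ANCOVA in a two-arm trial.

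Two stronger readings are tempting and not supported:

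- That the within-arm contrast is a more precise version of the planned one. The two estimate different quantities, so their interval widths or rejection rates are not a fair comparison.
- That the added estimates would explain a null pain result. The substudy is a short treadmill test of 40 volunteers in one standard shoe. The pain outcome reflects 12 weeks of everyday wear. Evidence on acute neutrality is supportive at most.

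This is a worthwhile, cost-free improvement to a secondary aim. The primary analysis and the sample size are unaffected.

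**What to change.** In the Statistical analysis section:

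1. Keep the ANCOVA for the biomechanical outcomes, name it as the lift-versus-sham comparison, and state that its covariate is the shoe-only value for the same gait.
2. Add, separately for walking and running, the insert-minus-shoe-only estimate with 95% CI in each arm for ankle plantar/dorsiflexion and Achilles tendon load, for example from a mixed model with arm, condition and their interaction. That is 2 arms x 2 gaits x 2 variables = 8 estimates, reported as estimates rather than as further confirmatory tests.
3. State how they will be read. The sham-arm estimate is supportive evidence on acute neutrality, judged by its interval and not by a non-significant p-value. The lift-arm estimate is the effect of the lift as worn, including any effect of the cover.

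The cost is two or three sentences. No new data, visits or participants are needed.
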